### Sample size

2.4

Sample size was calculated based on the primary outcome measure, the University of Wisconsin Running Injury and Recovery Index (UWRI) [12]. Using a power of 80%, previously reported standard deviation of 6.7 [13], medium effect size (Cohen's *d* = 0.75) of 5 points on the 36‐point UWRI [14] and a significance level set at *α* < 0.05, we estimated using GPower 3.1 (Kiel University, Germany) that a total of 60 participants (i.e., approximately 30 per group) will be required. When estimating sample size we were limited with data available and have opted to use the medium effect size for our estimation. To allow for any imprecision in these estimates, we will have a recruitment target of 32 participants per group.

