### Mixed effects analysis

3.2

A mixed effects model will be used to assess the mean differences between the groups for the outcomes considered. The fixed effects are between‐participant variables such as age, sex, BMI, symptom management and footwear. These models incorporate time as the random effects which is a within‐subject variable. All assumptions for mixed effects modelling will be checked. As most of the outcome measures will be considered as continuous, normality and homogeneity of variance assumptions will be assessed. If these assumptions are violated, alternative modelling approaches will be considered. Effect modification by age, BMI and sex will be explored using likelihood ratio tests, taking into consideration the sample sizes of the subgroups. Strata‐specific results will be reported if the *p* value for the interaction terms is < 0.1, and if at least one of the observed associations from the strata‐specific models are statistically significant at *p* ≤ 0.05. Results from these models will be presented as estimated effect sizes (both unadjusted and adjusted), standard errors, 95% confidence intervals and *p* values. All statistical analyses will be performed using the latest version of Stata (StataCorp, College Station,TX, USA).

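### Section 3.2: with 64 participants the likelihood ratio tests for effect modification run at about 11–13% instead of 10%, so the exploratory reporting gate is somewhat looser than stated

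*Protocol article*

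**What the plan says.** Section 3.2 (Mixed effects analysis) names the method for subgroups. Whether the group effect varies with age, BMI or sex "will be explored using likelihood ratio tests", and the section adds that subgroup sizes will be borne in mind. Strata-specific results are reported only if two conditions are both met. One is that the p "value for the interaction terms is < 0.1". The other applies within the strata, at the 5% level (p ≤ 0.05), and is met "if at least one of the observed associations from the strata‐specific models are statistically significant at" that level.

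On the model itself, the same section says: "The fixed effects are between‐participant variables such as age, sex, BMI, symptom management and footwear". Results are to be given unadjusted and adjusted, with "standard errors, 95% confidence intervals and" p values. No estimator, reference distribution or degrees-of-freedom method is named for those estimates or for the strata models. Likelihood ratio tests are mentioned for effect modification only.

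On size, section 2.4 says "we will have a recruitment target of 32 participants per group", which makes 64 in all.

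**The concern.** A likelihood ratio test of a fixed effect needs maximum likelihood fits of the two nested models and refers twice the log-likelihood difference to chi-square. Two approximations enter. Maximum likelihood divides the between-participant sum of squares by N and not by N minus the number of coefficients, so the variance is underestimated. The chi-square reference also ignores that this variance is estimated. Both make p values too small. Repeated visits do not help, because a group-by-sex, group-by-age or group-by-BMI term carries information only between participants.

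The p < 0.1 threshold decides, with the second condition, which subgroup results are reported. If the test behind it runs above 10%, more false interactions pass than the threshold suggests. This can happen for three modifiers and every outcome analysed.

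**Working it through.** **The plan's own figure.** Section 2.4 uses a difference of 5, SD 6.7, 80% power and α 0.05, so d = 5/6.7 = 0.746. The normal approximation gives 29 per group. The noncentral t distribution (two-sided) gives power 0.797 at 29 and 0.811 at 30 per group, so 30 per group. The stated total of 60 is reproduced, and N = 64 is the recruitment target.

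**Inputs.**
- N = 64 (section 2.4); nominal level 0.10 (section 3.2).
- Coefficients p. The smallest interaction model has intercept, group, modifier and interaction: p = 4. With all five listed covariates as one term each, plus intercept, group and interaction: p = 8. The list is introduced by "such as" wording ("variables such as age, sex, BMI, symptom management and footwear"), so p is an assumption and a range is shown.
- Assumed: complete balanced visits, normal errors, a random intercept, covariates constant over time, a one-degree-of-freedom interaction.

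**Interaction test.** Under these assumptions a between-participant effect is tested as in a regression on participant means, with t on N − p degrees of freedom, and

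LR = N · log(1 + t²/(N − p)).

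The test rejects when LR > 2.7055, that is when t² > (N − p)(e^(2.7055/N) − 1). For N = 64, e^(2.7055/64) − 1 = 0.04318.

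| p | t² cut-off | \|t\| cut-off | df | true size at nominal 10% |
|---|---|---|---|---|
| 4 | 60 × 0.04318 = 2.591 | 1.610 | 60 | 11.3% |
| 6 | 58 × 0.04318 = 2.504 | 1.583 | 58 | 11.9% |
| 8 | 56 × 0.04318 = 2.418 | 1.555 | 56 | 12.6% |
| 10 | 54 × 0.04318 = 2.332 | 1.527 | 54 | 13.3% |

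The exact 10% cut-off is 1.671 at 60 df and 1.673 at 56 df. A simulation of random-intercept maximum likelihood fits (64 participants, 3 visits, intraclass correlation 0.6 assumed, 4000 replicates) gave 11.7% with no added covariates (p = 4) and 13.4% with four (p = 8). The simulation margin is about ±1 point (1.96 × √(0.134 × 0.866/4000) = 0.011), so formula and simulation agree.

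**Conditional figures, which the document does not establish.** If the reported results came from maximum likelihood with a Wald z statistic, the test would reject when |t| > 1.960 · √((N − p)/N):
- N = 64, p = 2 (unadjusted): cut-off 1.929 on 62 df, size 5.8%.
- N = 64, p = 7 (intercept, group, five covariates): cut-off 1.850 on 57 df, size 7.0%.
- N = 32, p = 6 (one stratum, modifier dropped): cut-off 1.767 on 26 df, size 8.9%.

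Likelihood ratio tests in the same three cases give 5.5%, 6.6% and 8.0%. With restricted maximum likelihood and t on N − p df, each is 5%.

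**The joint gate.** Take two equal strata, global null, independent standard normal stratum statistics z1 and z2, and interaction statistic (z1 − z2)/√2. By simulation, both conditions are met 4.9% of the time at nominal levels, 5.5% with the interaction test at 12.6%, and about 7.5% if the strata tests also ran at 8%.

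**The case against.** The best case for leaving the text alone has four parts.

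- **It is exploratory.** The 0.1 and 0.05 values form a reporting filter and are not promised error rates. The joint gate opens less than 10% of the time in every case above. This stands, and it limits the point to a minor one. The gate still opens more often than the stated thresholds imply.
- **Estimator and degrees of freedom belong in the analysis plan.** This is true of anything left unstated. Here, though, the protocol commits to a named test, so an analysis plan using small-sample F tests would depart from it.
- **The section already says that subgroup sizes will be considered.** It gives no method, and the remark does not alter the reference distribution of the named test.
- **The likelihood ratio test is conventional, and the coefficient count is not fixed.** Both are true. Even the smallest interaction model, however, runs at 11.3%.

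A reader might go further and infer that the UWRI comparison is tested at 7%, that its 95% intervals cover only 93%, or that strata tests run at 8–12%. The document does not support this. It names likelihood ratio tests for effect modification alone, and using maximum likelihood for those tests does not commit the authors to it for the reported estimates. Section 3.1 also compares groups at each time point with t tests, which carry a small-sample reference. Nor can it be assumed that every stratum has 32 or fewer participants: any unequal two-way split of 64 leaves one above 32, and no male/female split or age and BMI cut-points are given.

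**Conclusion.** The point holds for the interaction tests and is minor. At a nominal 10% their true size is about 11.3% with 4 coefficients and 12.6% with 8, an excess of roughly 1 to 3 points. This rests on 64 participants with balanced visits, normal errors, a random intercept and time-constant covariates; the upper figure also needs all listed covariates entered as single terms. Missing data, time-varying symptom management or a different random-effects structure would change the exact values.

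The practical consequence is a slightly looser exploratory filter: for one modifier and one outcome, the joint gate moves from about 4.9% to 5.5% when only the interaction test is inflated. Figures for the treatment effect and the strata models remain conditional on an estimation method that the document does not state. Nothing here shows an error in the primary comparison.

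**What to change.** In section 3.2, replace the likelihood ratio tests with restricted maximum likelihood fits and Kenward-Roger or Satterthwaite t or F tests of the interaction terms. State that the same degrees-of-freedom method is used for the reported confidence intervals and p values and for the strata-specific models, and label the subgroup results as exploratory. In the balanced normal case this returns the nominal 10% and 5% levels. It also matches section 3.1, which already turns to a Satterthwaite approximation for the t tests.

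The cost is a sentence in the text and model options in the analysis code, with no change to conduct or sample size. Intervals become slightly wider and p values slightly larger. Compared with maximum likelihood and a normal reference, an adjusted interval with 7 coefficients would be about 8% wider (2.002/1.960 × √(64/57) = 1.08).

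### Subgroup results are shown only after passing two significance thresholds, so those that are reported will on average exaggerate the subgroup difference unless the true interaction is very large

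*Protocol article*

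**What the plan says.** Section 3.2 (Mixed effects analysis) states: "Effect modification by age, BMI and sex will be explored using likelihood ratio tests, taking into consideration the sample sizes of the subgroups". It then sets two conditions, joined by a conjunction, for showing results by stratum. The first is that the p "value for the interaction terms is < 0.1". The second reads "and if at least one of the observed associations from the" strata-specific models is significant at p ≤ 0.05. The next sentence lists the presentation format (unadjusted and adjusted effect sizes, standard errors, 95% confidence intervals, p values). It does not lift the conditions on the strata-specific results, and nothing elsewhere in the article provides for showing strata that fail them.

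The planning figures are in section 2.4 (Sample size): a "previously reported standard deviation of 6.7" on the UWRI, an effect "of 5 points on the" 36-point scale, and a target of 32 participants per group.

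**The concern.** An estimate that is published only if it is statistically significant is biased away from the null, and more so when power is low. A trial sized for a main effect has little power within halves of its sample, so the estimates that pass tend to be those that chance has pushed far apart.

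The article calls this the first randomised trial of running retraining in MTSS, and its Discussion says likely responders cannot currently be identified. A stratum result shown under this rule could be taken as evidence of who responds. The reader would have no matching stratum estimates for the modifiers that failed the thresholds.

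**Working it through.** **Inputs.** From section 2.4: SD 6.7, effect 5 points, α 0.05, power 80%, 32 per group. From section 3.2: interaction threshold 0.1, stratum threshold 0.05, three modifiers. Stratum sizes are not given. I assume two equal strata, so 64 / 2 strata / 2 arms = 16 per arm per stratum, and vary this below.

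**The protocol's own figure.** d = 5/6.7 = 0.746. A two-sided two-sample t test with 80% power needs 29.18, so 30 per group and 60 in total, as stated. (Sidedness is not stated; two-sided reproduces the figure.) The sample size is not at issue.

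**What a stratum must show to pass.**
- SE of a stratum effect = 6.7 × √(2/16) = 2.37. With t(30) = 2.042, the estimate must exceed 2.042 × 2.37 ≈ 4.8 points, almost the whole 5-point design effect. Power within a stratum for 5 points is 53%.
- With 12 or 8 per arm, the required estimate is 5.7 or 7.2 points and power is 42% or 29%.
- SE of the difference between strata = 6.7 × √(4/16) = 3.35. With t(60) = 1.671 for p < 0.1, strata must differ by about 1.671 × 3.35 = 5.6 points. The likelihood ratio test is slightly more lenient at this sample size: it passes 11.2% of the time with no interaction.

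**Simulation of the rule.** 400,000 trials per scenario, 32 per arm, likelihood ratio interaction test at p < 0.1, within-stratum t tests at p ≤ 0.05, strata reported only if both conditions hold. This is a single-time-point approximation to the mixed model.

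| True stratum effects | Result given that the rule reports |
|---|---|
| 0 and 0 | reported 5.1% of the time; significant stratum averages 5.6 in absolute size |
| 5 and 5 | reported 11%; significant stratum averages 8.2; absolute contrast 6.7 (truth 0) |
| 5 and 0 | strata average 6.9 and −1.2; contrast 8.1 (truth 5) |
| 7.5 and 2.5 | strata average 9.0 and 1.1; contrast 7.9 (truth 5) |
| 10 and 0 | contrast 10.6 (truth 10) |

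**Comparison with no rule.** With no true interaction, the mean absolute contrast without any selection is 3.35 × √(2/π) = 2.7 points, from sampling error alone. The rule raises it to 6.7. With true effects of 5 and 0, reporting everything gives mean estimates of 5.0 and 0.0, an unbiased contrast of 5.0. The rule gives 8.1, about 1.6 times the truth.

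**Three modifiers.** If they are independent, the chance that at least one is reported for a given outcome is 1 − (1 − 0.051)³ = 14.5% with no effect, and 1 − (1 − 0.11)³ = 29.5% with a uniform 5-point effect.

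**Which threshold matters.** With true effects of 5 and 0, dropping only the stratum condition leaves a contrast of about 7.9. Most of the bias comes from conditioning on the interaction p value, so removing the second condition alone is no cure.

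**Unequal strata.** With true effects of 5 and 0, splits of 20/12 and 24/8 per arm give reported contrasts of 8.2 and 8.9, the same pattern.

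**The case against.** The strongest defence is that the analysis is prespecified, names its three modifiers, is described as exploratory and takes subgroup size into consideration. No aim or conclusion of the trial concerns a subgroup. The rule does not treat a within-stratum p value as proof of effect modification, because the interaction test must pass first. The second condition makes reporting rarer: with no effect, it cuts the rate from 11.2% to 5.1%. All of this stands. It limits data dredging and the harm done, but it does not remove the bias in what is eventually shown.

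Four stronger readings are tempting, and the document does not support them.
- A reader might infer that every reported subgroup effect, or nearly every one, is spurious or overstated. With true effects of 10 and 0 the reported contrast exceeds the truth in only 55% of reported cases, and with 7.5 and 0 in 70%.
- A reader might multiply the rates over all outcomes to count expected false subgroup claims. Section 3.2 does not say which outcomes will be analysed by subgroup, and nothing supports assuming the design effect on each of them.
- A reader might infer that the interaction tests themselves are withheld. Only strata-specific results are explicitly conditional; whether interaction results are always shown is not stated.
- A reader might infer that age and BMI will be dichotomised. No cut-points are given, and an interaction term can be continuous.

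The choice of summary also matters. The larger of two stratum effects averages 2.7 points when the truth is 0, and 6.3 when it is a uniform 5, with no selection rule at all. That measure would overstate what the rule adds, so the argument here rests mainly on the contrast between strata.

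**Conclusion.** The point holds, as a statement about averages. The rule selects subgroup results on significance, and at this trial's size the selected contrasts are materially exaggerated when the true interaction is absent or modest: an absolute 6.7 against 0, and 8.1 against 5. The bias is small when the interaction is very large (10.6 against 10).

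These figures rest on assumed strata of 16 per arm, the planning SD of 6.7, complete data on 64 participants and a single-time-point approximation. A smaller residual SD from the mixed model would shrink the bias in points but would not alter the 5% rate when there is no effect. The primary comparison at week 4 is untouched; what is at risk is any statement about who benefits.

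**What to change.** Replace the two-threshold sentence in section 3.2 with wording to this effect: for at least the primary outcome, treatment-by-sex, treatment-by-age and treatment-by-BMI interaction estimates will be reported with 95% confidence intervals irrespective of their p values and labelled exploratory; age and BMI will preferably enter as continuous variables; p values within strata will not determine which results are shown. If stratum estimates are wanted, for sex for example, show all of them with confidence intervals.

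The cost is a change of wording in the analysis plan and one supplementary table. Recruitment, conduct and the primary analysis do not change.

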## DISCUSSION

4

This is the first randomised controlled trial to determine the effectiveness of running retraining in the management of MTSS in runners. Although laboratory‐based studies have previously shown that running retraining strategies can be used to decrease tibial loads [29, 30, 31], there is a lack of evidence for whether it provides improvements in pain and function for runners with MTSS.

The running retraining intervention (cueing a shorter step length) and its implementation was selected for this trial for three main reasons. Firstly, a relationship between reducing running step length and reducing tibial load and the probability of a tibial bone stress injury [5] has been well reported [5, 31], and the consequence of increasing the number of loading cycles by increasing the number of steps does not appear to increase injury risk [5]. Research has also indicated that kinematic factors such as the orientation of the hip, knee and ankle for a given stride length may be critical when considering the magnitude of tibial acceleration [31]. Secondly, despite the widespread understanding of an inverse relationship between decreasing step length and increasing step rate, data from our previous study indicates differences in the implementation of these cues, with a reduction in step length having a preferred effect on tibial loads at both a comfortable and moderate running pace [4]. Thirdly, the implementation of the running retraining strategy is designed to provide participants with adequate feedback to retrain their running gait, including both acquisition and transfer phases to assist with motor skill learning [32]. This will be achieved via real‐time haptic feedback from a Garmin running watch that monitors step rate while running, and verbal and visual feedback via 2D video footage at various timepoints in the trial. As the selected running watch is commercially available and widely used by runners, it should enable our running retraining intervention and its implementation to be readily utilised in the management of MTSS in runners if it is found to be effective in this trial.

Previous studies investigating running retraining to reduce tibial loads have found real‐time visual feedback [29, 30], haptic feedback [33], and clinician verbal feedback [29] are all effective in reducing tibial loads. Whilst these studies have demonstrated that running retraining can be effective in reducing tibial loads, none have examined the clinical effectiveness of running retraining among runners with MTSS. In addition, there is an absence of studies investigating the effects of running retraining on tibial loads beyond immediate effects. Despite this, running retraining is a common strategy adopted by clinicians and coaches in the management of running related lower‐leg pain [3]. With few running retraining trials conducted for running‐related injuries, the expected rates and types of adverse events remain somewhat unknown. However, as the cue to reduce step length will likely result in minimal changes to other gait parameters [4] the risk of adverse events is considered negligible.

Whilst ‘best standard care’ for MTSS has not yet been established, a clinical trial by Mendez‐Rebolledo and colleagues found that the inclusion of 6 weeks of neuromuscular training (plyometric and weightbearing drills) in uninjured female athletes reduced the incidence of MTSS [34]. To our knowledge, the effect of a strength training program inclusive of plyometric exercises on runners with MTSS has yet to be investigated. The inclusion of ‘best standard care’ as a comparator intervention assists with accounting for non‐intervention effects (e.g., placebo effect, Hawthorne effect, natural resolution, etc.) not directly related to the running retraining intervention. Providing participants with an intervention that they perceive as being equally credible and expected to provide similar benefits as the experimental intervention will assist in minimising confounding factors such as resentful demoralisation among participants not receiving the running retraining. As all participants will spend a similar amount of time with clinicians, receive the same number of appointments, their experience in the trial is expected to be very similar (with the only exception being the inclusion of running retraining).

The eligibility criteria do not require participants to have a particular running gait pattern. Although running retraining is most likely used in a clinical setting to change a gait parameter believed to be associated with MTSS, it is not currently possible to identify individuals with MTSS most likely to benefit from running retraining. In addition, decreasing step length has been shown to reduce tibial loads in uninjured runners with no pre‐specified gait characteristics, for example, a long baseline step length [4]. Since a specific gait parameter is not an inclusion criterion, it is possible that not all participants included in our trial will potentially experience a reduction in tibial loads by reducing their step length. Although any expected improvements in pain and function is proposed to result from a reduction in tibial load, it is also possible that a clinical benefit may result from another mechanism of action related to a reduction in step length that currently remains unknown.

This trial has been designed to optimise its scientific rigour while ensuring a high clinical utility. Some strengths of the trial include the use of allocation concealment, blinded data entry, adhering to the intention‐to‐treat principle to analyse data, and the use of a comparator intervention as a control. In addition, this trial has been designed to have high external validity, with the eligibility criteria being representative of a demographic most likely to experience MTSS, and the study being conducted in a real‐world setting, ensuring any findings regarding the success of interventions can be transferable to clinical practice. If effective, the gait retraining program's use of a commercially available wearable device ensures that our findings will be reproducible and will translate readily to clinical settings. However, due to the nature of the interventions, inherent limitations with this trial are a lack of blinding of the primary investigator and blinding of participants via limited disclosure. We acknowledge the potential for clinician bias, and plan to address this by ensuring a similar amount of time is spent with each participant, that the duration of each data collection session be recorded to allow a comparison at the conclusion of the trial, and that an assessor blinded to group allocation be involved in all decision making regarding best standard care and progression of load. Accordingly, the findings of this trial will need to be viewed in consideration of its strengths and limitations.

